### End Points

The primary end point is wound closure by day 5, by suture, flap, or split-thickness skin graft.

The coprimary end point is net clinical benefit, defined as a composite of wound closure by day 5 and freedom from any bleeding, infection, sepsis, or loss of index limb.

The secondary end points are (1) rate of wound healing, defined as days to wound closure by suture, flap, or split-thickness skin graft; (2) wound infection, defined as purulent discharge [15]; (3) wound size ratio at day 14 (wound size day 14 compared with size day 0, ie, wound healing rate after 14 days); (4) time until wound is deemed no longer requiring professional care; (5) number of surgeries; (6) time to hospital discharge; (7) quality-of-life aspects; (8) wound healing at follow-up days 14 and 30, and at 3 months; (9) bleeding leading to blood transfusion; (10) sepsis; (11) limb amputation (limb with wound included in the study); (12) death; (13) direct health care costs (substudy); and (14) cost effectiveness (substudy).

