### Randomization and Blinding

We use a computer-generated randomization code with random variation of 2 fixed block sizes to achieve balance in the allocation of participants to the 2 treatment arms and reduce the opportunity for bias and confounding. Each site has its own dedicated randomization list respecting the 1:1 ratio. The sealed randomization envelopes are opened by the operating room nurse at the end of the first surgery, but before the wound dressing is applied. By randomizing after the operation, we eliminate the risk of treatment allocation influencing the surgeon’s choice of debridement technique. Wound photographs will be evaluated by 2 independent trained evaluators who are blinded to the treatment allocation. Due to the nature of the treatment methods, blinding of the patients or staff involved in the treatment would not be possible.

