### Sample Size and Power Calculation

The sample size calculation was based on detection of a difference of 25% between treatment groups in the proportion of patients for the primary outcome. We estimated the expected rate of patients reaching the primary outcome at day 5 to be 75% in the NPWT group and 50% in the control group. Based on a power of 80% and a significance level of 5%, we calculated that we would need a minimum sample size of 116 patients (58 per group) to detect a significant difference in the proportions. To adjust for dropouts, we aim to include 200 patients (100 per group).

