### Data Collection

Dedicated research nurses collect and enter data into paper-based case report forms during the study period. For all enrolled patients, contact details including mobile phone number are collected. Wounds are photo documented at day 0, at every dressing change, at day 14, and, if possible, at 1 and 3 months’ follow-up. Photo documentation is done in a standardized way with a single-colored background and an adhesive paper ruler attached to the edge of the wound.

**Table 1 table1:** Timeline of trial activities.

Time point	Activity
Baseline	Patient inclusion (consent within 5 days of randomization), patient details, injury details, wound details, photograph of wound, SRQ-20^a^ scores, and quality-of-life details
End of first surgery	Randomization, allocation of treatment, wound details, treatment details, photograph of wound
Dressing change	Treatment details, wound details, photograph of wound
Hospital discharge	Treatment details, wound details, SRQ-20 scores, and quality-of-life details
Day 14	Treatment details, wound details, photograph of wound
Day 30	Treatment details, wound details, photograph of wound
3 months	Treatment details, wound details, photograph of wound

^a^SRQ-20: 20-item Self Reporting Questionnaire.

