### Statistical Analysis

We will perform analyses on an intention-to-treat basis with a 2-sided significance level of .05. The primary end point (wound closure by day 5) will be presented as proportions with a 95% confidence interval for the difference in proportions. We will analyze the coprimary end point with standard survival analysis using proportional hazards for comparison of the treatment arms. For the primary end point, we will also perform a per-protocol analysis, excluding patients who did not receive the planned treatment or did not survive to day 5. We will report baseline characteristics as means and standard deviations or numbers and percentages, as appropriate. Subgroup analyses will include age, injury mechanism, initial injury severity, associated fracture versus no fracture, and initial wound size.

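### Randomisation is stratified by site, but the primary analysis as stated names neither site nor baseline wound size, so its interval may be somewhat wider than needed.

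*Protocol article*

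**What the plan says.** The End Points section makes the primary outcome binary: "The primary end point is wound closure by day 5, by suture, flap, or split-thickness skin graft".

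Under Randomization and Blinding: "Each site has its own dedicated randomization list respecting the 1:1 ratio". With blocks inside each list, the arms are kept balanced within site. The Setting section describes two sites: Ar Ramtha, Jordan, enrolling from June 2015, and Erbil, Iraq, enrolling from May 2017. They have different operators and patient streams. The split of patients between them is not given.

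The Statistical Analysis section fixes the general rule, "We will perform analyses on an intention-to-treat basis with a 2-sided significance level of .05", and then the primary summary: "The primary end point (wound closure by day 5) will be presented as proportions with a 95% confidence interval for the difference in proportions". Initial wound size appears in that section only in the list of subgroups.

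Wound size is available for every planned patient. Table 1 lists, for the end of the first surgery, "Randomization, allocation of treatment, wound details, treatment details, photograph of wound", and one secondary end point uses the day-0 size as its denominator.

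**The concern.** When randomisation is balanced within strata that predict the outcome, the between-stratum variation cancels out of the treatment comparison. A standard error that ignores the strata still counts that variation, so it is too large for the design that was run. The interval is then a little wide and the test a little conservative. A strong baseline predictor that was not used in randomisation works in a related way: leaving it out does not bias the difference, but adjusting for it would remove variance.

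Both kinds of variable are at hand. Different closure rates at the two sites are plausible, because dressing technique and the interval between changes are left to the treating clinicians. The article reports no rates by site. What is at stake is efficiency, and it matters most if the effect is smaller than planned or if losses take the sample towards the stated minimum.

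**Working it through.** **1. The plan's own figure.** The Sample Size section assumes an "expected rate of patients reaching the primary outcome at day 5 to be 75% in the NPWT group and 50% in the control group", with 80% power and a 5% level, taken as two-sided. With p̄ = 0.625 and Δ = 0.25:

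n per arm = [1.96·√(2·0.625·0.375) + 0.8416·√(0.75·0.25 + 0.50·0.50)]² / 0.25² = (1.342 + 0.557)² / 0.0625 ≈ 57.7, rounded up to 58.

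This matches the stated "minimum sample size of 116 patients (58 per group"). Power by the same pooled formula is 80.2% at 58 per group and 96.0% at 100 per group.

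**2. Unadjusted interval.** SE = √[(0.1875 + 0.25)/n]. At n = 100 this is 0.0661, a half-width of 13.0 points. At n = 58 it is 0.0869, a half-width of 17.0 points. The power figures below use this unpooled SE, which is why they start at 96.6% and 82.1%.

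**3. Site only.** Assume a gap g in closure rate between sites, the same in both arms, and a share w of patients at one site. The within-site variance sum is 0.4375 − 2·w(1 − w)·g². For g = 0.30 and w = 0.5 it is 0.4375 − 0.045 = 0.3925, so the stratified SE at 100 per arm is 0.0626. The unadjusted SE is 0.0661/0.0626, or about 5.6% larger.

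Under site-balanced allocation the true spread of the estimate is SE_strat. Power is therefore Φ[(0.25 − 1.96·SE_unadj)/SE_strat] for the unadjusted test and Φ[0.25/SE_strat − 1.96] for the stratified one.

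| Site gap (equal split) | Half-width, 100 per arm | Narrower by | Power at 100 per arm, unadjusted / stratified | Power at 58 per arm, unadjusted / stratified |
|---|---|---|---|---|
| 0 | 13.0 | 0% | 96.6 / 96.6% | 82.1 / 82.1% |
| 10 points | 12.9 | 0.6% | 96.6 / 96.7% | 82.2 / 82.5% |
| 20 points | 12.7 | 2.3% | 96.9 / 97.2% | 82.6 / 83.8% |
| 30 points | 12.3 | 5.3% | 97.3 / 97.9% | 83.4 / 86.0% |

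With an 80:20 split the 30-point gap narrows the interval by 3.3%.

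**4. Wound size only.** Assume a normal covariate on a suitable scale, with a constant effect on the log-odds scale and marginal rates held at 75% and 50%. With m₁ and m₀ the closure probabilities given wound size, the standardised risk difference has large-sample variance V/N, where V = E[2m₁(1 − m₁) + 2m₀(1 − m₀) + (m₁ − m₀ − 0.25)²]. Without adjustment V is 2·0.4375 = 0.875.

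| Odds ratio per SD | Half-width, N = 200 | Narrower by | Worth, in patients | Power, N = 200 | Power, N = 116 |
|---|---|---|---|---|---|
| 1.0 | 13.0 | 0% | 200 | 96.6% | 82.1% |
| 1.25 | 12.9 | 0.5% | 202 | 96.7% | 82.5% |
| 1.5 | 12.7 | 1.7% | 207 | 97.0% | 83.4% |
| 2.0 | 12.4 | 4.5% | 219 | 97.7% | 85.4% |
| 2.5 | 12.0 | 7.1% | 232 | 98.3% | 87.3% |
| 3.0 | 11.7 | 9.4% | 244 | 98.7% | 88.8% |

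**5. Both together.** In 4,000 simulated trials per scenario with N = 200, the mean full width, adjusted versus unadjusted, was:
- 25.9 versus 25.8 points when neither was prognostic
- 25.4 versus 25.8 at odds ratio 1.5 and a site log-odds of 0.4
- 24.7 versus 25.8 at odds ratio 2 and a site log-odds of 0.4
- 23.8 versus 25.8 (about 8% narrower) at odds ratio 2.5 and a site log-odds of 0.8

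Coverage of the unadjusted interval stayed between 94.7% and 95.3%.

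**6. Behaviour of a plain stratified Wald test.** In 200,000 simulated trials under the null, with 50 per arm per site and closure of 35% and 65% at the two sites, it rejected 5.3% of the time, against 4.5% for the unadjusted test.

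**The case against.** The strongest reply is that the article does not call its analysis crude, unadjusted or pooled. It says how the result will be presented, and a Mantel-Haenszel risk difference would also fit that sentence. An analysis plan that is not shown may supply the strata and covariates. This stands as far as intent goes: nobody can say the investigators decided against adjustment. It does not remove the point. The section does fix the summary measure, interval, significance level, analysis set and subgroup variables. Read plainly, it describes a simple difference that does not follow the randomisation.

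A second reply is that nothing is invalid. That also stands. Under randomisation the simple difference is unbiased, and ignoring the strata errs on the conservative side. It was the plain stratified Wald test that ran slightly above 5%.

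A reader might go further and infer that the interval is needlessly wide, or that much power is being thrown away. The documents do not support this. If closure were 25% at one site and 75% at the other, with a 20-point effect, power would be 87% unadjusted and 93% stratified. But nothing in the article suggests a 50-point gap between sites, and its planned effect is 25 points. At that effect, a 30-point gap with equal enrolment costs 0.6 points of power at 100 per arm and 2.6 points at 58 per arm.

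Finally, adjusting for wound size, which was not a stratification factor, is a choice and not a requirement of the design. That is fair, and it makes site the firmer half of the recommendation.

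**Conclusion.** The mismatch is real: allocation is stratified by site, and the stated primary analysis mentions neither site nor the baseline wound size that is collected. The consequence is a possible modest loss of precision, with no bias and no inflated error.

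Under the assumed ranges the loss is 0 to 5% of interval width from site at an equal split (0 to 3% at 80:20) and 0 to 9% from wound size. It is nil if neither predicts closure. With all 200 patients analysed the effect on power is minor. Near 116 patients it could be worth having, up to about 7 percentage points from wound size at the top of its range.

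Confidence is high in the mismatch. The size of the gain rests on site gaps, enrolment splits and a wound-size association that the article does not report.

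**What to change.** Before outcomes are compared by arm, prespecify one of these as the primary estimate:

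- a Mantel-Haenszel risk difference stratified by site, with a 95% interval method that holds its coverage in small strata, not a plain stratified Wald interval; or
- a logistic model with arm, site and baseline wound size, standardised to a risk difference with its 95% interval.

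Keep the unadjusted difference as a supportive analysis. Stratify the coprimary proportional hazards analysis by site. Fixing the choice in advance matters because treating staff are not blinded, and an adjustment chosen after the results are known would be open to challenge.

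The cost is a change of wording and a little more analysis work, with no new data to collect. There is no gain if site and wound size are not prognostic; in the simulation, adjusting then widened the interval by about 0.5%. The model version also depends on complete day-0 wound measurements, so it needs a stated rule for missing values. The site-stratified version does not have that dependence.

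### Net clinical benefit is defined as a yes/no status but analysed by proportional hazards with no event defined, so its hazard ratio depends on an unstated coding

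*Protocol article*

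**What the plan says.** The End Points section of the protocol article names net clinical benefit as the coprimary end point, "defined as a composite of wound closure by day 5 and freedom from any bleeding, infection, sepsis, or loss of index limb". It ties closure to day 5 and gives no separate window for the harm-free part.

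The Statistical Analysis section treats the two headline end points differently. The primary end point, closure by day 5, "will be presented as proportions with a 95% confidence interval for the difference in proportions". For the other: "We will analyze the coprimary end point with standard survival analysis using proportional hazards for comparison of the treatment arms". No section recasts net clinical benefit as a time to an event.

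The list of secondary end points does include true durations. The first is "rate of wound healing, defined as days to wound closure by suture, flap, or split-thickness skin graft". The Statistical Analysis section does not assign survival methods to it.

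**The concern.** A proportional hazards model compares the rate at which one defined event occurs. Net clinical benefit joins an event that is wanted (closure) with the absence of four events that are not. As written it is settled per patient as yes or no and carries no date. To fit the named model, someone must choose what counts as the event, when the clock starts and what censors a patient. The article makes none of these choices.

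This matters because the end point is coprimary. One of the two headline results would be a hazard ratio whose meaning depends on a later choice, in a trial where treating staff cannot be blinded. It is also more than detail that an article may leave to an analysis plan, because the article names the method and the method does not fit the article's own definition.

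**Working it through.** **Inputs from the protocol.** Closure by day 5 is expected "to be 75% in the NPWT group and 50% in the control group" (Sample Size and Power Calculation). The planned enrolment is 100 per group, the test is two-sided at 0.05, and dressing changes are generally 3 to 5 days apart (Interventions). The project's wound infection rate of 11% (Setting) is borrowed below only as an illustrative harm rate. All other rates are assumptions.

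**The plan's own figure.** For two proportions with pooled variance, two-sided 5% and 80% power:

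n = [1.96·√(2·0.625·0.375) + 0.8416·√(0.75·0.25 + 0.50·0.50)]² / 0.25² = (1.342 + 0.557)² / 0.0625 ≈ 57.7, so 58 per group.

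The stated 58 reproduces (power 80.2%). It rests on a comparison of proportions for the primary end point.

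**Coding 1, event = closure.** Two checks.

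- *Later harm is not seen.* Assume constant hazards, independent harm, closure 75% vs 50%, and 30-day harm of 11% in both arms. Net benefit is 0.75 × 0.89 = 66.8% vs 0.50 × 0.89 = 44.5%, a gap of 22 points. The closure hazard ratio is ln(0.25)/ln(0.50) = 2.0. Now raise harm to 30% in the negative-pressure arm only. Net benefit becomes 0.75 × 0.70 = 52.5% vs 44.5%, a gap of 8 points, and the closure hazard ratio stays at 2.0.
- *Timing alone moves it.* Let 60% close by day 5 in both arms, with 80% vs 40% of those closures on day 3 and the rest on day 5. Per 100 patients, 48 vs 24 close on day 3, and 12 vs 36 on day 5 from 52 vs 76 still open. With Breslow ties the hazard ratio θ solves 60 = 72θ/(1+θ) + 48·52θ/(52θ+76), giving θ = 1.16. Efron ties give 1.20. The closure proportions do not differ. At 1000 per arm the Efron p value is 0.0015 (z ≈ 3.18). At the planned 100 per arm z would be about 3.18/√10 ≈ 1.0, so the fault here is in what is estimated, not a sure false positive.

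**Coding 2, event = first harm.** In the case above with 11% harm in both arms, the hazard ratio is 1, although net benefit differs by 22 points. With 30% vs 11% harm it is ln(0.70)/ln(0.89) ≈ 3.1 against the negative-pressure arm, although net benefit still favours that arm by 8 points.

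**Coding 3, event = first harm, or unclosed at day 5 (dated day 5).** Both components now enter. Take closure 75% vs 50%, with one third of closed wounds in the first arm and none in the second harmed after day 5. Net benefit is 0.75 × 2/3 = 50% vs 50%. Per 100 patients, 25 vs 50 fail together at day 5, and 25 more fail later in the first arm only. With Breslow ties and distinct later times, θ solves 50 = 75θ/(1+θ) + Σ jθ/(jθ+50), summed over j = 51 to 75, giving θ ≈ 0.95. Efron ties give 0.83. The true difference is zero, and the answer changes with the tie method because three quarters of the events fall at one instant.

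**The case against.** A reader might infer that proportional hazards cannot estimate this end point at all, or that the planned model would return a hazard ratio of 1 whatever the net benefit. The protocol does not support either reading.

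- A hazard ratio of 1 is tied to a particular coding. Suppose closure is 60% in both arms and later infection among closed wounds is 11% vs 33%. Net benefit is 0.60 × 0.89 = 53.4% vs 0.60 × 0.67 = 40.2%. With equal closure times, closure coding gives 1, but coding 3 gives about 0.73 to 0.75. With closure 75% vs 50% and 11% harm in both arms, harm coding gives 1, but coding 3 gives about 0.47 to 0.49 (Efron) or 0.55 to 0.56 (Breslow).
- If every patient is given the same time, day 5, a Cox model with Breslow ties returns the risk ratio: 75 = 125θ/(1+θ) gives θ = 1.5 for 75% vs 50%.

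These points stand, and they rule out the word cannot. They do not rescue the sentence. Neither coding 3 nor the common-time device is described in the protocol. The second is hardly the standard survival analysis that it promises, and the first can still show an effect when net benefit is equal.

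Two further limits are fair. The worked rates show what is possible, not what is expected: 11% is a project-wide infection rate, not a rate for the four harms among closed wounds, and the 30% and 33% are invented. If day 5 is meant to bound the harms as well, little time remains for harm after closure and the examples with late harm shrink. Nor does the bunching of closures on a few days count against survival methods in general. Closure is a surgical act with a known date, and days to closure would bunch in the same way.

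**Conclusion.** The point holds as a mismatch between definition and method. A coprimary end point defined as a status is assigned a model that needs an event time, and the event is left undefined. The size of the distortion cannot be fixed from the protocol, because it depends on the coding, the harm window and the harm rates. Under the stated assumptions, the hazard ratio is 0.83 to 0.95 or 1.16 to 1.20 where the proportions compared are equal, and closure coding gives an unchanged 2.0 while the gap in net benefit falls from 22 to 8 points.

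The reach is limited to the coprimary end point. The primary end point, its analysis as proportions and the 58 per group are unaffected.

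**What to change.** Replace the sentence on the coprimary end point in the Statistical Analysis section. Net clinical benefit should be analysed in all randomised patients as a binary outcome, by a difference in proportions with a 95% confidence interval, as that section already does for the primary end point. In the End Points section, state the window over which bleeding, infection, sepsis and limb loss are counted, since without it the binary outcome is also open. Proportional hazards can be kept for days to wound closure.

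The cost is two edits to the text. The method change needs no new data and no extra patients, but the window must be one over which the harms are already recorded.

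The sample size was set for the primary end point only, so the power of the revised analysis depends on the share of closed wounds that stay free of harm. The protocol does not give that share; the table assumes it is equal in both arms, with 75% vs 50% closure and all 100 per group analysed:

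| Harm-free share | Net benefit | Power at 100 per group |
|---|---|---|
| 1.00 | 75% vs 50% | 96% |
| 0.95 | 71% vs 48% | 93% |
| 0.89 | 67% vs 45% | 89% |
| 0.80 | 60% vs 40% | 81% |
| 0.70 | 53% vs 35% | 71% |

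### The supplementary per-protocol analysis excludes patients who die by day 5, which makes it partly a survivors-only comparison and weakens it as a check on the intention-to-treat result

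*Protocol article*

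**What the plan says.** The Statistical Analysis section of the protocol article makes intention-to-treat the basis of the analyses: "We will perform analyses on an intention-to-treat basis with a 2-sided significance level of .05". For the primary end point only, it then adds a supplementary analysis: "we will also perform a per-protocol analysis, excluding patients who did not receive the planned treatment or did not survive to day 5". It gives no reason for the survival condition, and nothing elsewhere in the article qualifies it.

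The End Points section defines the outcome concerned: "The primary end point is wound closure by day 5, by suture, flap, or split-thickness skin graft". Death is listed there separately, as secondary end point 12. It is not a named component of the coprimary net clinical benefit, which is "defined as a composite of wound closure by day 5 and freedom from any bleeding, infection, sepsis, or loss of index limb". Under Randomization and Blinding, allocation takes place at the end of the first surgery, so every death that the rule can act on occurs after randomisation.

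**The concern.** A per-protocol set is meant to show what happens when patients receive what they were allocated. Failing to receive the planned treatment fits that purpose. Dying does not: a patient who had the allocated dressing and died on day 3 did not depart from the allocated treatment. The rule selects patients by an event that treatment could influence, and it does so inside the five days over which closure is measured.

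Most of those removed would probably have open wounds. They leave the denominator while the closures stay in the numerator, so the closure rate of an arm rises with its early deaths. The article itself names routes by which the arms could differ. Under Summary of Potential Risks and Benefits, it says the occlusive dressing might cause infections or delay their detection, mentions bleeding, and allows that conventional dressing might carry more health care–associated infection. A difference in deaths could therefore run either way.

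At stake is the use of the per-protocol result beside intention-to-treat. Agreement or disagreement between the two should reflect adherence. Under this rule it could reflect deaths.

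**Working it through.** **Inputs from the article.** Expected closure by day 5 is "75% in the NPWT group and 50% in the control group"; the planned enrolment is 100 per group and the minimum is 58 per group (Sample Size and Power Calculation).

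**The plan's own figure.** The stated minimum reproduces. With pooled rate (0.75 + 0.50)/2 = 0.625, two-sided 5% significance and 80% power:

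n = [1.960 × √(2 × 0.625 × 0.375) + 0.842 × √(0.75 × 0.25 + 0.50 × 0.50)]² / 0.25² = (1.342 + 0.557)² / 0.0625 ≈ 57.7, so 58 per arm and 116 in total.

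The point concerns the analysis set and disputes no stated figure.

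**Assumptions.** The article gives no early death rate. I take 0 to 10 deaths by day 5 per 100. At first I assume that nobody who died had reached closure. Under intention-to-treat they count as not closed, which follows from the definition of the end point.

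**Formula.** With x closures among n patients and d deaths, the rate is x/n if the deaths are kept and x/(n − d) if they are dropped. Dropping them multiplies the arm's rate by n/(n − d).

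**Closures 75/100 and 50/100.** Keeping the deaths gives 25.0 points (95% CI 12.0 to 38.0) however they are split. Dropping them gives:

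| Deaths, NPWT vs control | Rates after exclusion | Difference (points) |
|---|---|---|
| 2 vs 2 | 75/98 = 76.5%; 50/98 = 51.0% | 25.5 |
| 5 vs 0 | 75/95 = 78.9%; 50/100 = 50.0% | 28.9 |
| 10 vs 2 | 75/90 = 83.3%; 50/98 = 51.0% | 32.3 |
| 0 vs 5 | 75/100 = 75.0%; 50/95 = 52.6% | 22.4 |

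With equal deaths the difference still widens slightly, because the same multiplier acts on a higher rate.

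**A smaller effect.** With 62/100 and 50/100 closed, keeping the deaths gives 12.0 points (Wald 95% CI −1.7 to 25.7). Dropping 5 NPWT deaths against none gives 62/95 − 50/100 = 15.3 points (1.6 to 29.0). The interval then excludes zero only because patients in the NPWT arm died. With 2 deaths in each arm it is 12.2 (−1.5 to 26.0), and the reading does not change.

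**Equal closure among survivors.** With 10 against 2 deaths and half the survivors closed in each arm, keeping the deaths gives 45/100 − 49/100 = −4.0 points (−17.8 to 9.8). Dropping them gives 45/90 − 49/98 = 0.0.

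**If some who died had already closed.** With c closures among the d deaths, the rate after exclusion is (x − c)/(n − d). This exceeds x/n whenever c/d is below x/n. For 75/100 with 5 deaths, c = 2 gives 73/95 = 76.8%, still above 75%; c = 4 gives 71/95 = 74.7%, slightly below. The direction therefore depends on those who died having closed less often than the arm as a whole.

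**The case against.** The strongest reply is that little rests on this analysis. This is a superiority trial with intention-to-treat as its basis. The per-protocol analysis is additional, and its exclusion rule is stated openly in advance. That stands, and it limits the importance of the point.

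A reader might infer that the rule hides early mortality, or that it biases the primary result. The article supports neither. The exclusion applies only to the per-protocol analysis of the primary end point. No rule removes deaths from the intention-to-treat analysis, and death, sepsis and bleeding leading to transfusion are separate secondary end points. A very uneven split would also be visible there: 8 deaths against 0 in 100 per arm has a two-sided Fisher p of 2 × C(100,8)/C(200,8) ≈ 0.007. For 5 against 0 the same formula gives about 0.06, which is less striking but still visible in a table of deaths.

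It can also be said that someone who dies on day 1 or 2 has not completed the planned course, since the Interventions section has wounds treated until closure and dressings generally changed every 3 to 5 days. Interest in patients who could complete treatment is intelligible. But that is a survivors-only question, and calling it per-protocol conceals the difference.

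Finally, not every excluded death is a closure failure, because a patient whose wound closed before death is removed as well. That is correct, and the figures above state the assumption.

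**Conclusion.** The point holds for the per-protocol analysis alone. Survival to day 5 is an outcome after randomisation, and conditioning on it favours the arm with more early deaths, provided that those who died had closed less often than their arm as a whole. The per-protocol result is then an unreliable check on intention-to-treat.

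The size depends on a death rate that the article does not give. At 100 per arm with no closures among those who died, a true 25.0-point difference is reported as anything from 22.4 to 32.3 points across the splits tabulated. If deaths are few and balanced, the shift is about half a point and can be ignored. A changed reading, as in the 62 against 50 case, needs both an uneven split and a borderline result. The clause should be corrected, but no primary conclusion of the trial depends on it.

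**What to change.** In the Statistical Analysis section, delete the condition on survival to day 5, so that the per-protocol set is defined by treatment received only. Within that set, count patients who die before closure as not closed, and keep as closed those whose wound closed before they died. Show the number of deaths by day 5 in each arm beside the result.

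If a comparison among survivors is still wanted, keep it as a separate, further analysis under that name, with the deaths by arm next to it.

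The intention-to-treat analysis needs no change on this account. The cost is one deleted clause, one sentence on how deaths are counted, and one added row in a table. Closure and death are already end points of the trial, so no new data are needed.
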